## Abstract

**Background:**

The German welfare system follows the principle “rehabilitation rather than pension,” but more than the half of all disability pensioners did not utilize medical rehabilitation before their early retirement. A major barrier is the application procedure. Lack of information about the opportunity to utilize rehabilitation services restricts the chance to improve work ability and to prevent health-related early retirement by rehabilitation programs. The establishment of new access paths to medical rehabilitation services was, therefore, identified as a major challenge for rehabilitation research in a recent expertise. Thus, a web-based information guide was developed to support the application for a medical rehabilitation program.

**Methods/Design:**

For this study, the development of a web-based information guide was based on the health action process approach. Four modules were established. Three modules support forming an intention by strengthening risk perception (module 1), positive outcome expectancies (module 2) and self-efficacy (module 3). A fourth module aims at the realization of actual behavior by offering instructions on how to plan and to push the application process. The study on the effectiveness of the web-based information guide will be performed as a randomized controlled trial. Persons aged 40 to 59 years with prior sick leave benefits during the preceding year will be included. A sample of 16,000 persons will be randomly drawn from the registers of 3 pension insurance agencies. These persons will receive a questionnaire to determine baseline characteristics. Respondents of this first survey will be randomly allocated either to the intervention or the control group. Both study groups will then receive letters with general information about rehabilitation. The intervention group will additionally receive a link to the web-based information guide. After 1 year, a second survey will be conducted. Additionally, administrative data will be used to determine if participants apply for rehabilitation and finally start a rehabilitation program. The primary outcomes are the proportion of applied and utilized medical rehabilitation services. Secondary outcomes are cognitions on rehabilitation, self-rated work ability, health-related quality of life and perceived disability, as well as days with sick leave benefits and days of regular employment.

**Discussion:**

The randomized controlled trial will provide highest ranked evidence to clarify whether theory-driven web-based information supports access to rehabilitation services for people with prior sickness benefits.

**Trial registration:**

German Clinical Trials Register (Identifier: DRKS00005658, 16 January 2014).

**Electronic supplementary material:**

The online version of this article (doi:10.1186/s13063-015-0968-7) contains supplementary material, which is available to authorized users.

## Background

Many Western welfare systems provide rehabilitation services to improve work ability and to support participation in working life. In Germany, these services are provided usually as 3-week inpatient or outpatient programs under the umbrella of the German Pension Insurance (GPI). The treatment is multi-professional and follows evidence-based therapy standards [1]. The legal framework of the German rehabilitation system, which regulates access to and the organization of services, is based on the notion of preventing permanent work disability by the provision of rehabilitation services [2]. However, in 2013 58.6 % of all male and 51.9 % of all female first-time disability pensioners did not use rehabilitation services before their health-related early retirement [3]. In many cases the concept of “rehabilitation rather than pension” apparently does not work [4].

One main reason for non-utilization seems to be that medical rehabilitation requires a formal application of the person in need. A current study revealed that about one third of the disability pensioners were not informed on the possibility of claiming a medical rehabilitation program due to limitations in work ability [5]. If need for rehabilitation does not lead to an application of medical rehabilitation, the opportunity of preventing permanent work disability and the receipt of disability pensions remains unused. Though the Social Security Code explicitly states that guidance and motivation to use medical rehabilitation are obligatory if disabled people are in need (§26, Subsection 3, Sentence 7, SGB IX), there is obviously a lack of professional information on how to claim a medical rehabilitation [6]. The exploration and testing of new access paths to medical rehabilitation services were, therefore, identified as major challenges for rehabilitation research [7].

One potential gate for information might be web-based information guides [8]. These provide the advantage of easy access, even for persons having only scarce time resources or living in rural or in isolated areas. To use web-based information guides, only Internet access and a stationary or mobile Internet device is needed [9]. Recent studies point out the easy accessibility of the Internet among the working aged population and showed its relevance as a source for information search. In 2014, 94 % of Internet users aged 30 to 49 years and users aged ≥ 50 years utilized the Internet for seeking information [10]. Furthermore, web-based information services are less costly than compared with conventional information which makes use of paper, compact-discs or similar mediums [9].

Additionally, web-based information guides have the potential to support e-health literacy if they provide evidence-based information in a comprehensible format. This might help to handle the information flood of the Internet which often is perceived to be diffuse or overtaxing [11–13]. As a consequence, the relevance of the Internet as a medium of health-related information and interventions has substantially increased during recent years [9, 14–18].

In a qualitative study, Sillence et al. [13] examined factors supporting user acceptance and confidence in web-based information guides. Fussy layouts, confusing navigation, too much text and pop-ups increased rejection and mistrust towards a website. Web-based information guides were positively rated if they included interactive elements, e.g. assessments, clear and simple language, a section for frequently asked questions and unbiased information. Information provided by web-based guides, which were designed accordingly, was recognized as similarly important as information provided by relatives or physicians. However, general practitioners and specialists were still the first choice if a final decision was needed. These findings are in line with recent randomized controlled trials. Web-based information guides increased disease knowledge and health literacy and contributed to a reduction of uncertainty, anxiety and decision conflicts [19–22]. However, though web-based information seems to assist and prepare the decision-making process, it does not necessarily lead to a higher frequency of reached decisions either in favor of, or against, the intervention of interest than compared to a control group [19, 23].

Against this background we developed a web-based information guide promoting the application for rehabilitation services. The information guide aims at raising the frequency of applications for and utilization of medical rehabilitation services in persons who experience restrictions in their work ability. This study protocol describes the design of a randomized controlled trial which was developed to clarify whether the anticipated higher rates of applications and utilization will be achieved.

## Methods

### Design

The study will be performed as a randomized controlled trial.

## Treatment

### Control

Participants in the control group will receive a letter which informs about the general aims of medical rehabilitation and the possibility to apply for a medical rehabilitation program. The complete wording of the letter is available as Additional file 1.

### Intervention

Participants in the intervention group will also receive an informative letter. The first section of this letter equals the letter of the control group. In addition, the participants will be informed on a web-based information guide, obtain a link to the corresponding webpage and will be invited to use the web content in order to verify a potential need for rehabilitation and to claim a medical rehabilitation program. The complete wording of the letter is available as Additional file 2.

The development of the web-based information guide was based on the health action process approach (HAPA) [24]. According to the HAPA, health-related behavior change is described to be a process which consists of two phases: a motivational and a volitional phase. The motivational phase covers the growth of an intention to engage in a specific behavior. The volitional phase describes how an intention can be facilitated to turn into a specific behavior. During the motivational phase, the realization of an intention depends on the individual risk perception on what would happen without doing something, outcome expectancies in case of a specific behavior option and finally the level of perceived self-efficacy to act accordingly.

In the case of rehabilitation claims, Zimmermann et al. [25] reported that 41 % of persons with a self-rated need for rehabilitation intended an application for medical rehabilitation, and only 11 % of the persons with a subjective need finally applied for a rehabilitation program within 1 year. In a more recent study, Mittag et al. [26] reported comparable results. There seems to be both a lack of intention probably due to an information gap [6, 27] and a so-called intention-behavior gap. The first, the information gap, is partly reasoned by the segmented German health care system with different insurance schemes for primary health care and rehabilitation. Thus, important actors in the primary health care sector like the general practitioners have only limited knowledge and skills on the procedures which are needed to claim rehabilitation services [6]. The latter, the intention-behavior gap, refers to the well-known observation that an intention is not sufficient for realizing a specific behavior [28–30]. In this context, recent findings from health psychology research indicate that action planning is needed to translate health-related intentions into actual behavioral outcomes [24, 31, 32].

Thus, the web-based information guide was designed for supporting both, forming an intention and planning the application for medical rehabilitation. We therefore developed four modules. Modules 1 to 3 support the formation of an intention by strengthening risk perception (module 1), positive outcome expectancies (module 2) and self-efficacy (module 3). The realization of an actual behavioral outcome, e.g. a formal rehabilitation claim, is focused by the fourth module. This module includes structured instructions in order to support the planning of a rehabilitation claim (Fig. 1).

**Fig. 1 Fig1:**
[figure not shown]
Conception of the web-based information guide

Staff members of the participating pension insurance agencies were consulted during the developmental process to include practical experiences and to consider the legal framework of the application process. Separate webpages were designed for each participating pension insurance agency because there are slight differences in some of the procedures and application forms. The web-based information guides are available at the web addresses http://www.reha-jetzt.de, http://www.reha2015.de and http://www.reha2016.de.

#### Module 1: completing the work ability index

Module 1 offers the option to evaluate the individual need for rehabilitation. To assess the potential need for rehabilitation the German version of the Work Ability Index (WAI) will be used.

The WAI was developed by the Finnish Institute of Occupational Health in the mid-1980s. It is available in 26 languages and internationally the most common instrument to assess work ability. The WAI measures the degree to which persons consider their state of health as adequate to cope with their job demands [33]. The WAI yields a score from 7 to 49, where higher scores indicate better work ability. These scores can be classified into 4 categories: poor (7–27), moderate (28–36), good (37–43) and excellent work ability (44–49) [34]. The authors of the WAI recommended tailored interventions for these categories, e.g. measures improving or restoring work ability if the current WAI is categorized as moderate or poor. According to the German social welfare system regulatory framework, both lower categories correspond with a need for rehabilitation [4].

Recent studies confirmed that the WAI is a predictor for the need for rehabilitation and rehabilitation-related impairments of functional capacity also within the setting of the German welfare system [4, 35]. These results are in line with international studies which identified the WAI as an important predictor of disability pension [36–38].

After completing the WAI the individual total score will be automatically calculated, and participants will receive a brief explanation and a concluding recommendation. The feedbacks are summarized in Table 1.

**Table 1 Tab1:** Recommendations according to self-reported work ability

Work Ability Index: 37 to 49 points
Your work ability is good or excellent. At this moment, you do not have any health problems which significantly impair you in managing your daily work demands. You currently do not need a medical rehabilitation. But will it stay this way? The risk of coming down with chronic diseases increases with age. You should be prepared! Talk to your general practitioner or your occupational physician about opportunities how you can maintain your health and work ability.
Work Ability Index: 28 to 36 points
Your work ability is moderately limited. You suffer from health problems which make it difficult for you to cope with your daily work demands. Maybe you already stop enjoying work or worry about your future. A medical rehabilitation may support you in your current situation. Applying a rehabilitation is less laborious than what one might suppose. Our instructions will make it easy for you to master the application process. You will find the instructions right here.
Work Ability Index: 7 to 27 points
Your work ability is severely restricted. You suffer from health problems which make it impossible for you to cope with your daily work demands. Studies have shown that persons with low scores as yours have a remarkably high risk for premature retirement. But it is not too late to avoid this. You need a holistic treatment as provided by a medical rehabilitation program to manage your health problems. Applying a rehabilitation is less laborious than what one might suppose. Our instructions will make it easy for you to master the application process. You will find the instructions right here.

Persons with good or very good work ability currently do not have a need for rehabilitation. In this case the participants will receive recommendations how to maintain their work ability in cooperation with their general practitioner or their occupational physician. Participants with moderate work ability will be informed about medical rehabilitation as an option to improve the current work ability. If the WAI indicates poor work ability, participants will also receive a recommendation to apply for medical rehabilitation. Additionally, the participants are informed about the urgent need in order to avoid a disability pension. In both cases of recommendation for rehabilitation participants will be directly forwarded to the step-by-step instructions on how to apply for a medical rehabilitation.

#### Module 2: reports of positive experiences by rehabilitants

To strengthen positive outcome expectancies, reports of successful medical rehabilitation by former rehabilitation users will be presented. These reports shall strengthen the perception that rehabilitation is an effective option for the participants to sustain their work ability.

The reports are based on interviews which we conducted with former rehabilitants. Interview partners were recruited in five stationary rehabilitation centers and five ambulant rehabilitation centers. The guided interview dealt with the main diagnosis, personal pathways to rehabilitation, progress of health problems before, during and after medical rehabilitation and self-rated success factors of medical rehabilitation. Eleven guided interviews were conducted via phone and examined using content analysis [39]. For presentation on the webpage, contents were summarized as brief experience reports and enriched with original quotations from the interview. All experience reports are presented anonymized on the webpage. The experience reports were published only if the interview partners provided informed consent and agreed on using the interviews as examples at our web-based information guide. Participants of the intervention group may select and read each report individually.

#### Module 3: information on medical rehabilitation

In this module all relevant information on medical rehabilitation under the umbrella of the GPI and the application procedures are summarized in a clear and structured way. The content includes aims and types of rehabilitation as well as the legal framework and practical aspects, e.g. assumption of costs, continued payment of wages, additional payments and childcare facilities. In this way the participants will be prepared for the application process and be made aware of access barriers and information myths. The information section is hyperlinked to the step-by-step instructions and a frequently asked questions section (FAQ section). The FAQ section is designed dynamically. Participants may ask questions using a contact form which will be answered by mail. Questions and answers will successively complete the FAQ section. Additionally, a search function was implemented for accessibility of each section of the webpage by entering a search term.

#### Module 4: step-by-step towards the rehabilitation application

The step-by-step instructions shall reveal that the way towards an application for a rehabilitation program is manageable and that formal obstacles and the temporal expenditure can be mastered. The instruction traces the complete path of the application process until the start of the rehabilitation program and thus strengthens action planning by decomposing the complex task of a rehabilitation claim. Each required form is named and explained regardless of whether it has to be completed by the applicant herself or himself, by the attending physician, the health insurance or the employer. By this, participants will keep track of their documents and can control the application process (e.g. making an appointment with the attending physician for the medical statement which is needed). The description of the forms provides detailed explanations on how to complete them. Each administrative term and the function of the information that is to be given by the applicant will be explained. Additionally, a hyperlink is provided to download the corresponding form. All in all, the participants receive a comprehensive overview of the complete application process. This also includes the steps following the approval.

### Participants

Persons aged 40 to 59 years with prior sick leave benefits and regular employment of at least 6 months in the year before the beginning of the study will be included. Exclusion criteria are the receipt of pension benefits and the receipt of medical or vocational rehabilitation services during the last 4 years. Samples are randomly drawn from the registers of three pension insurance agencies, i.e. the federal agency and two regional agencies. Sampling will be stratified by pension insurance agency, sex and duration of sick leave benefits.

Persons will be informed about purpose and intervention of the study, its duration and data protection. Participation in the study will be consented by answering the questionnaire of the initial survey. Consent for using administrative data of the participants will be obtained by signature on the informed consent form during the second survey.

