### Randomization

A postal survey on baseline characteristics will be sent to potential participants. Respondents to this first survey will be randomly allocated to the intervention and the control group. Randomization will be conducted by a statistician of the Institute of Social Medicine and Epidemiology, University of Lübeck, who is not otherwise involved with the trial, by using computer-generated random numbers. Allocation will be stratified by a pension insurance agency.

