### Sample size estimation

To detect a 10-point higher rate of applications for a medical rehabilitation program (controls: 50 %), 1,076 persons (538 per group) are needed relying on a 2-sided alpha error of 0.05 and a power of 0.90. Response rates of 30 % to the first survey and of 50 % to the second survey were assumed to calculate the gross sample size to be drawn from the insurance registers. We finally decided to draw 8,000 persons for both the federal agency and the two regional agencies to allow segmented analyses according to the type of agency. Sample drawing was stratified by sex and the duration of sickness benefits in the year prior to the first survey (15 to 30 days versus more than 30 days).

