### Data management

The insurance agencies generate numeric pseudonyms as unique identification numbers for all randomly selected individuals. The insurance agencies will post the pseudonymized questionnaires to the sampled individuals. Persons will be informed that in case of participating in the first survey they will be randomly allocated either to the intervention or the control condition. Participants will then send back their questionnaires to the researchers. After the first survey is completed, random assignment will be performed, and participants will obtain their corresponding intervention letter. Intervention letters for both the participants of the control group (see Additional file 1) and the intervention group (see Additional file 2) are available for more details. One year later, a second survey will be conducted. Moreover, the insurance agencies will provide administrative data on rehabilitation events to the researchers if participants give their approval. The numeric identification numbers will be used by the researchers to match questionnaire and administrative data. Consequently, researchers’ access to personal data of the sampled individuals (e.g. addresses and insurance account numbers) is avoided. Additionally, access and utilization of the webpage will be documented during the study period and provided as aggregated data by the open analytics platform Piwik (http://piwik.org).

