## Outcome measures

### Main study outcome

The primary outcomes are the proportion of applied and utilized medical rehabilitation services after 1 year in the intervention group as compared to the control group. These data will be extracted from the individual GPI accounts.

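### Consent to the register data behind both primary outcomes is signed only at the 1-year survey, so inclusion in the primary comparison is decided after allocation and can bias it in either direction

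*Protocol article*

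**What the plan says.** Two separate consents are described in the Participants section of the protocol article. Taking part needs no signature: "Participation in the study will be consented by answering the questionnaire of the initial survey". Use of the register data does: "Consent for using administrative data of the participants will be obtained by signature on the informed consent form during the second survey".

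The other sections fix what follows from this:

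- Randomization: "Respondents to this first survey will be randomly allocated to the intervention and the control group".
- Main study outcome: the one-year proportions of people who applied for and who used rehabilitation are compared between arms, with the source given as "These data will be extracted from the individual GPI accounts".
- Data management: "One year later, a second survey will be conducted", and "the insurance agencies will provide administrative data on rehabilitation events to the researchers if participants give their approval".
- Sample size estimation: response rates of 30 % to the first survey and 50 % to the second "were assumed to calculate the gross sample size to be drawn from the insurance registers". No rate is given for signing among those who reply.

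The article describes no other route to the account data of a randomised person who does not reply to the second survey or does not sign.

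**The concern.** The agencies draw the sample, generate the pseudonyms and hold the accounts from which both primary outcomes are extracted, so the outcomes could in principle be nearly complete. The timing of consent makes them incomplete. A person enters the primary analysis only by returning a questionnaire and signing a form a year after the letters, when it is already settled whether that person used the guide, applied or attended.

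Reply and signature may plausibly depend on both arm and outcome. Only the intervention letter offers the guide, which is built to strengthen self-efficacy and to help people complete forms. Someone who applied with its help may have a different reason to return a rehabilitation survey and release the data than a control who applied without it. If so, the groups compared are not the groups that were randomised, and the difference in proportions mixes the effect of the guide with a difference in who volunteers. Selection could create an apparent effect or hide a real one.

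**Working it through.** **1. The plan's own figure.** Inputs (Sample size estimation): 50 % versus 60 %, two-sided alpha 0.05, power 0.90. The normal-approximation formula for two proportions gives 519 per group without continuity correction and 538 with it. The stated 538 per group (1,076) is reproduced exactly with the correction. Gross sample: 1,076 / (0.30 × 0.50) = 7,173.3, so 7,174, in line with drawing 8,000 per agency type. The arithmetic is sound and already allows for the number of people lost.

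**2. Planned flow.** 16,000 × 0.30 = 4,800 randomised, about 2,400 per arm. 4,800 × 0.50 = 2,400 second-survey responders. This is the upper limit for people with a known primary outcome, before any loss from not signing.

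**3. When selection biases the comparison.** Let p be the true application rate in an arm, a the reply-and-sign rate of its applicants and b that of its non-applicants. Then

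observed rate = p·a / (p·a + (1 − p)·b), or equivalently observed odds = true odds × (a/b).

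The observed odds ratio is therefore the true odds ratio multiplied by (a/b in the intervention arm) / (a/b in the control arm). With no true effect:

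- Applicants reply more than non-applicants by the same ratio in both arms: no bias.
- One arm replies more overall, whatever the outcome: no bias.
- The ratio a/b differs between arms: bias.

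With a true effect, equal ratios preserve the odds ratio but shift the absolute difference a little. For example, at 60 %/40 % in both arms, true rates of 50 % and 60 % are observed as 60 % and 69.2 %, a difference of 9.2 points and not 10.

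**4. Illustration (assumed rates).** No true effect, 2,400 randomised per arm, reply-and-sign 50 % for everyone except intervention applicants. True rates: 11 % (the one-year application rate that the Intervention section cites for people with a self-rated need), 50 % (the planning control rate) and 20 % as an assumed value between them. The last column is the rejection probability of the uncorrected two-sided 5 % two-proportion test.

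| Intervention applicants | True rate | Observed intervention rate | Spurious difference | False-positive rate |
|---|---|---|---|---|
| 55 % | 11 % | 0.0605/0.5055 = 12.0 % | +1.0 | 12 % |
| 55 % | 20 % | 0.110/0.510 = 21.6 % | +1.6 | 16 % |
| 55 % | 50 % | 0.275/0.525 = 52.4 % | +2.4 | 22 % |
| 60 % | 11 % | 0.066/0.511 = 12.9 % | +1.9 | 31 % |
| 60 % | 20 % | 0.120/0.520 = 23.1 % | +3.1 | 46 % |
| 60 % | 50 % | 0.300/0.550 = 54.5 % | +4.5 | 63 % |

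If intervention applicants reply less readily than the rest, the sign reverses.

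**5. Overall reply rates may not reveal it.** In the 60 % scenario at a true rate of 11 %, overall return is 51.1 % against 50.0 %. A second scenario has identical overall return: true rate 50 % in both arms, 55 % for applicants and 45 % for non-applicants in the intervention arm, 50 % for all controls. Observed rates are 55 % and 50 %, and the false-positive rate is about 0.69 with 1,200 per arm.

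**6. Secondary note: no factor for signing.** Power for 50 % versus 60 %, uncorrected test:

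| Signing among responders (assumed) | All agencies | Power | One agency type | Power |
|---|---|---|---|---|
| 100 % | 2,400 | above 99 % | 1,200 | 94 % |
| 80 % | 1,920 | 99 % | 960 | 88 % |
| 70 % | 1,680 | 98 % | 840 | 83 % |

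**The case against.** The strongest reply is that the article gives no reply or signing rate by arm or by outcome. Both arms receive a rehabilitation letter with the same first section, and they differ only in the invitation to the guide. Many selection patterns do no harm under the null, as step 3 shows, and every row of the illustration puts the selection in one cell. This stands. The figures show sensitivity to assumed rates and do not predict what will happen.

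Four stronger readings are tempting, and the document does not support them:

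- That randomisation is lost, or that the test will find an effect where none exists. Outcome-dependent reply alone is not enough. The ratio has to differ between arms, and the article neither shows nor excludes that.
- That half the outcomes are bound to be missing. The 50 % is a planning assumption, and actual response may be higher or lower.
- That the trial is underpowered because signing was not counted. Overall power stays near 98 % at 70 % signing. The article says that the larger draw allows analyses by agency type, but it does not expressly promise 90 % power in each.
- That a method for missing outcomes is absent. Weighting or sensitivity analyses may be in an analysis plan that is not shown.

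What the objection does not answer is the timing itself. The protocol fixes it, and an analysis plan can respond to it but cannot undo it. Enlarging the draw replaces lost numbers but not lost comparability. With more people, a biased difference reaches significance more easily.

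**Conclusion.** The concern holds as a design weakness. The plan ties availability of both primary outcomes to behaviour one year after allocation. On its own 50 % assumption, they would be known for at most about 2,400 of about 4,800 randomised people. The chi-squared comparison can be biased in either direction. Under no true effect, that requires the applicant-to-non-applicant ratio of reply-and-sign rates to differ between arms. A difference of 5 to 10 percentage points in one cell, which is an assumption, is enough for a spurious difference of about 1 to 4.5 points and a false-positive rate of about 12 to 63 % instead of 5 %. The problem is bias. Loss of precision is a side note that matters, if at all, only for the analyses by agency type. The article's claim to provide evidence of the highest rank depends on a comparison of the groups as randomised, which this consent timing does not secure.

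**What to change.** 1. **People not yet surveyed.** Put the consent form for administrative data, as an optional sheet, in the first-survey mailing, before allocation. Define the primary analysis set as all randomised people who signed it, whether or not they answer the second survey. Refusal before allocation cannot depend on arm.

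2. **People already surveyed or randomised.** The Trial status section says that recruiting is ongoing, so step 1 comes too late for some. If data-protection rules allow, ask the agencies for anonymous counts of applicants and of people who started rehabilitation, by arm and agency, for everyone randomised. Report these as a key sensitivity analysis. Whether the rules permit this cannot be judged from the article.

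3. **Sample size text.** Add an assumed signing rate among those asked.

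**Cost.** An ethics amendment, one more sheet in the first mailing and a data request to each agency. No extra participants are needed. The main downside is that asking for a signature may lower first-survey response, by an amount the article gives no basis to estimate. There is room for this. At an assumed 70 % signing at either time, the plan yields 4,800 × 0.50 × 0.70 = 1,680 analysable people and baseline consent yields 4,800 × 0.70 = 3,360. First-survey response could fall from 30 % to 15 % before the two were equal (16,000 × 0.15 × 0.70 = 1,680).
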